# Early motion and directed exercise (EMADE) versus usual care post ankle fracture fixation: study protocol for a pragmatic randomised controlled trial

**DOI:** 10.1186/s13063-018-2691-7

**Published:** 2018-05-31

**Keywords:** Ankle, Fracture, Early rehabilitation, Exercise, Physiotherapy, Health economics

## Abstract

**Background:**

Following surgical fixation of ankle fractures, the traditional management has included immobilisation for 6 weeks in a below-knee cast. However, this can lead to disuse atrophy of the affected leg and joint stiffness. While early rehabilitation from 2 weeks post surgery is viewed as safe, controversy remains regarding its benefits. We will compare the effectiveness of early motion and directed exercise (EMADE) ankle rehabilitation, against usual care, i.e. 6 weeks’ immobilisation in a below-knee cast.

**Method/design:**

We have designed a pragmatic randomised controlled trial (p-RCT) to compare the EMADE intervention against usual care. We will recruit 144 independently living adult participants, absent of tissue-healing comorbidities, who have undergone surgical stabilisation of isolated Weber B ankle fractures. The EMADE intervention consists of a non-weight-bearing progressive home exercise programme, complemented with manual therapy and education. Usual care consists of immobilisation in a non-weight-bearing below-knee cast. The intervention period is between week 2 and week 6 post surgery. The primary outcome is the Olerud and Molander Ankle Score (OMAS) patient-reported outcome measure (PROM) at 12 weeks post surgery. Secondary PROMs include the EQ-5D-5 L questionnaire, return to work and return to driving, with objective outcomes including ankle range of motion. Analysis will be on an intention-to-treat basis. An economic evaluation will be included.

**Discussion:**

The EMADE intervention is a package of care designed to address the detrimental effects of disuse atrophy and joint stiffness. An advantage of the OMAS is the potential of meta-analysis with other designs. Within the economic evaluation, the cost-utility analysis, may be used by commissioners, while the use of patient-relevant outcomes, such as return to work and driving, will ensure that the study remains pertinent to patients and their families. As it is being conducted in the clinical environment, this p-RCT has high external validity. Accordingly, if significant clinical benefits and cost-effectiveness are demonstrated, EMADE should become a worthwhile treatment option. A larger-scale, multicentre trial may be required to influence national guidelines.

**Trial registration:**

ISRCTN, ID: ISRCTN11212729. Registered retrospectively on 20 March 2017.

**Electronic supplementary material:**

The online version of this article (10.1186/s13063-018-2691-7) contains supplementary material, which is available to authorized users.

## Background

### Background and rationale

Ankle fractures are extremely common, accounting for over 20% of all lower-limb fractures [1] . The AO (Arbeitsgemeinschaft für Osteosynthesefragen) system of open reduction and internal fixation (ORIF) technique, has become the accepted treatment for unstable ankle fractures [2]. The traditional post-surgery management has been based on 6 weeks’ non-weight-bearing, with the ankle immobilised in a below-knee cast.

Detrimental sequelae of this traditional regimen are a combination of joint stiffness, reduced range of motion (ROM), pain, reduced circulation, oedema and muscle atrophy [3–6]. This presentation has been termed ‘fracture disease’ [2, 7, 8] and ‘cast disease’ [7, 9–12]; the term ‘cast disease’ is used through the remainder of this protocol. Attempts to address cast disease can necessitate extended rehabilitation, but even so, not all patients obtain the desired recovery [13]. The necessity of delaying rehabilitation for 6 weeks is being increasingly questioned.

Systematic reviews of previous randomised control trials (RCTs) conclude that early rehabilitation is safe, citing no statistical difference between early rehabilitation and control groups in terms of fixation failure, delayed and non-union and rates of infections. [13–20]. An exception has been where rehabilitation was started immediately after surgery [21], yielding an unacceptable wound infection rate of 66%, in comparison to 16% in the control group. In contrast, delaying rehabilitation until at least 10 days post surgery resulted in a wound infection rate of just 9% [22].

While timing appears to be the single biggest risk factor for iatrogenic wound infections, the reviews identify ambiguity surrounding the evidence supporting effectiveness of early rehabilitation due to risk of methodological bias. For example, underpowered sample sizes and inadequacies in reporting of interventions and results [13–20]. The Cochrane reviewers concluded that while early rehabilitation is mostly safe, there is only ‘limited evidence’ on its effectiveness [13].

Early interventions can be classed broadly as early weight-bearing, early exercises or a combination of both. While NICE [23] recommend further research on early weight-bearing, the impact of early exercise remains an important and under-investigated regimen. Where there has been a focus on exercise as the intervention, it has mostly been limited to range of motion. A comprehensive training programme [24] has shown some benefit over a minimal programme, while in contrast, no supporting evidence was identified by Moseley et al. [4] for the addition of stretches and no supporting evidence for the addition of manual therapy by Lin et al. [25]. However, interventions for these studies commenced after the 6-week period, by which time cast disease would have been established.

We propose that an effective way to address the multifactorial condition of cast disease is the application of a multifactorial physiotherapy intervention. Developed through expert consensus this intervention is based on early motion and directed exercises (EMADE). To determine if the EMADE intervention is effective, it is being assessed against the current usual care for this condition. The EMADE protocol is presented in accordance with Standard Protocol Items: Recommendations for Interventional Trials (SPIRIT) and Template for Intervention Description and Replication (TIDieR) guidelines (see Additional files 1 and 2, respectively).

## Methods/design

### Aim

We aim to establish if, for Weber B ankle fracture patients who have undergone open reduction and internal fixation, whether the EMADE intervention is more effective in reducing symptoms and restoring function than usual care.

#### Primary objective

The primary objective of this study is to test the hypothesis that the early motion and directed exercise (EMADE) physiotherapy intervention, applied in the clinical setting, will perform better than usual care at 12 weeks following operative fixation for Weber B fracture as measured by the Olerud and Molander Score (OMAS) [26].

#### Secondary objectives include

A key secondary objective is to determine whether, in this patient group, EMADE will perform better than usual care in the short term (12 weeks post surgery) as measured by the EQ-5D-5 L quality of life measure and the Ankle-Fracture Outcome of Rehabilitation Measure (A-FORM)To determine whether, in this patient group, EMADE will perform better than usual care, in the medium- and long-term (24 and 52 weeks post surgery, respectively), as measured by the OMAS, EQ-5D-5 L and A-FORMTo explore the cost-effectiveness of EMADE

### Trial design and study setting

This is a prospective, pragmatic randomised controlled trial (p-RCT) of superiority design, with participants allocated in a 1:1 ratio to either of two parallel groups. The trial is based in the fracture clinic of the Queen’s Medical Centre, Nottingham University Hospitals, Nottingham, UK, with other sites being considered.

## Participants, interventions and outcomes

### Recruitment

The clinical care team will identify potential participants from hospital consultant and theatre lists and notify the researchers of those patients willing to be approached. A researcher will approach the potential participant and inform them of all aspects of the study and provide a written information sheet (available via http://www.isrctn.com/ISRCTN11212729). This states that entry is voluntary and that they are free to withdraw at any time without effect on subsequent care. If appropriate, following screening and following the opportunity to make an informed decision, written consent will be obtained from those willing to be recruited to the study. Consent will be re-confirmed verbally at each stage of the study.

### Eligibility

#### Inclusion criteria

Patients with isolated, closed Weber B fractures (AO44-B1, -B2 or -B3) which are stable following open reduction and internal fixation. This includes those requiring syndesmosis stabilisationPatients aged 18 years and overIndependently livingCapable of independently reading and completing the study paperwork in English

#### Exclusion criteria

Inability to provide informed consent, or declining participationComorbidities: diabetes requiring prescription drugs, non-healing leg/foot ulcers, oral or intravenously administered steroid users, pre-existing ankle arthritis and concurrent or history of significant ipsilateral or contralateral lower limb injury/condition, e.g. prosthesis in lower-limb joints, or neurological disordersAt the 2-week clinic visit a patient may be excluded if, based on individual clinical decision, there is notable risk that early wound movement will impede satisfactory healing.Those unable to commit to weekly clinic visits, if assigned to the EMADE intervention group

### Interventions

Pre-operatively and, during the first two post-operative weeks, participants receive identical care consisting of admission to hospital and consultant supervised surgery including management on a standard care pathway. Participants are discharged home in a cast and reviewed 2 weeks following surgery. All participants undergo x-ray post surgery and wound inspection following cast removal during the 2-week review (10 to 19 days post surgery). All participants are non-weight-bearing throughout the study until the 6-week point.

The EMADE intervention is a progressive home exercise programme that includes range-of-motion (ROM) and strengthening exercises, and is conducted by the participant up to six times a day. To be able to conduct the exercises, at the 2-week fracture clinic review, those in the EMADE intervention group are fitted with a removable below-knee cast with Velcro retaining straps.

The EMADE programme starts with light intensity and low daily repetitions, and as the weeks progress, becomes progressively more intensive and repetitive. For example, exercises start resistance-free, and are followed by elastic-exercise-band resistance; while the daily repetitions start twice daily and build up to six times daily. These progressions are taught during weekly face-to-face sessions between the week-2 and week-6 fracture clinic reviews.

During the physiotherapy sessions, participants receive manual therapy consisting of 5 to 10 min of joint and soft-tissue manipulation to the ankle complex. Advice and education is on-going and includes; healing processes, control of pain and swelling, and expectations of fluctuation of pain and swelling. These sessions take part in the recruiting hospital, and are provided by an experienced physiotherapist trained in the application of the EMADE intervention.

To encourage compliance with the EMADE home exercise programme, participants are provided with written and pictorial exercise sheets. These were developed through patient input and include diary sheets, although completion of the diary sheets is neither mandatory nor used in data collection. Participants are not paid to attend, but a basic travel allowance is offered to attend the additional sessions for the study, but not for usual NHS care. Participants in the usual care group are treated in a below-knee cast and remain non-weight-bearing until the 6-week point.

From the 6-week review, all study participants receive the same standard care. This includes removal of cast and, if appropriate following x-ray, weight-bearing as tolerated may commence, along with physiotherapy as required. Protocol deviations will be as per standard care, being based on individual clinical decisions.

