### Participant timeline

Recruitment and consent may take place from the in-patient stay until and including the 2-week post-surgery outpatient review. Only after all baseline outcome measures are recorded, does randomisation take place, see Figs. 1 and 2.

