**Fig. 2 Fig2:**
[figure not shown]
A schematic diagram of the patient’s journey through the early motion and directed exercises (EMADE) ankle study. Key: *EMADE* early motion and directed exercise, *PROMs* patient-reported outcome measures

The data collection time points (post surgery) are: baseline at 2 weeks, end of intervention at 6 weeks, and at three research follow-up time points; 12 weeks and 24 weeks as short- and mid-term follow-ups, respectively, and at 52 weeks as a long-term follow-up and the trial end point. For participant’s convenience, the 2-week and 6-week EMADE sessions are combined with the orthopaedic 2-week and 6-week reviews. The 12-week, 24-week and 52-week PROMs data may be collected via either return post (postage pre-paid), electronically or in person according to participant choice. Participants undergoing objective assessment will attend the David Greenfield Human Physiology Unit, Medical School, University of Nottingham, UK.

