Adjustment for baseline scores, through analysis of covariance, will be conducted for OMAS, EQ-5D-5 L and A-FORM and compared with unadjusted scores. Impact of covariates will be further explored through regression analysis. Initial analysis for co-variates where significance is nearly reached (*p* > 0.10) will be taken forward into a statistical model. Due to the bimodal impact of age and sex, these will be included in this analysis. Other exploratory analysis for potential covariates may include impact of smoking, previous level of physical activity, type of fracture (AO classification), complexity of surgical repair and any subsequent removal of metal work; most notably removal of syndesmosis screw(s) for which stratification was applied at randomisation. Analysis will also be conducted using modified ITT by excluding those participants who attend only one session or less of EMADE sessions.

Sub-groups will include return to work for those unable to work due to their ankle fracture at the time of randomisation, and similarly, return to driving for those unable to drive due to their ankle fracture at the time of randomisation. Frequency of complications will be described but, based on the published literature, it is anticipated that frequency will be sufficiently low not to warrant statistical analysis.

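### Between the week-2 and week-6 reviews EMADE participants are seen weekly and controls stay in a cast, so raw complication frequencies may mix detection with treatment

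*Protocol article*

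**What the plan says.** All references are to the protocol article.

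- **Week 2, both arms (Interventions).** "All participants undergo x-ray post surgery and wound inspection following cast removal during the 2-week review". The review falls 10 to 19 days after surgery. No other wound inspection is named.
- **Randomisation (Participant timeline).** "Only after all baseline outcome measures are recorded, does randomisation take place". The text under Fig. 2 sets the time points as "baseline at 2 weeks, end of intervention at 6 weeks". Exclusion criteria also allows exclusion at the 2-week visit on wound-healing grounds.
- **Weeks 2 to 6, EMADE (Interventions).** The cast is removable. "These progressions are taught during weekly face-to-face sessions between the week-2 and week-6 fracture clinic reviews". Each session includes 5 to 10 minutes of manual therapy to the ankle.
- **Weeks 2 to 6, usual care (Interventions).** Participants are in a below-knee cast. No visit is described before week 6.
- **Week 6, both arms (Interventions; Secondary outcome measures).** "This includes removal of cast and, if appropriate following x-ray, weight-bearing as tolerated may commence". Ankle movement, figure-of-8 and calf circumference are measured in both arms.
- **Harms (Secondary outcome measures; Governance).** Adverse events and x-ray findings are recorded, under reporting procedures that the article mentions but does not detail.
- **Analysis of harms (Data processing).** "Frequency of complications will be described". The article expects too few events to justify a statistical test.

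**The concern.** Wound infection is the harm that the article itself links to early movement. Background and rationale says "While timing appears to be the single biggest risk factor for iatrogenic wound infections" and cites infection rates of 66%, 16% and 9% from earlier studies. Any effect of EMADE on wounds can only appear after randomisation, and the first four weeks after it are the intervention period. In that period one arm is looked at regularly and can look for itself, while the other arm's wound is covered.

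A superficial problem that settles before week 6 has a good chance of being noted in EMADE and a smaller one in usual care. If the counts are set side by side without regard to how events came to light, an excess in EMADE could be a treatment effect, better detection, or both. With no test planned and few events expected, readers will judge safety from raw counts, where a difference of two or three events shapes the impression.

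**Working it through.** **1. Does the named inspection precede allocation?** Baseline is at 2 weeks, randomisation follows baseline, and wound condition at the 2-week visit can exclude a patient. Together these place the inspection before allocation. This is an inference from three statements; the article does not say it outright.

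**2. How unequal is scheduled contact between the two common reviews?** Discussion puts the extra cost of EMADE at about £54 to £75. Health economics gives £18 to £25 per session.

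- Lower end: 54 / 18 = 3 sessions.
- Upper end: 75 / 25 = 3 sessions.

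The text under Fig. 2 says the week-2 and week-6 EMADE sessions coincide with the orthopaedic reviews, so these three fall in between. Scheduled contacts in the window are therefore 3 in EMADE and 0 described in usual care.

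**3. Arm size for the illustration.** The inputs from Sample size calculations are a difference of 10 points, SD 19.5, significance level 5% (taken as two-sided) and power 80%.

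n per arm = 2 × (1.960 + 0.842)² × 19.5² / 10² = 2 × 7.85 × 3.80 = 59.7, rounded up to 60. The total is 120, which reproduces the article's figure; power at 60 per arm is 80.2%.

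**4. What unequal detection could do.** Let p be the true rate in both arms (no treatment effect), with every event detected in EMADE and a share s detected in usual care.

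- Expected recorded events: 60p in EMADE and 60ps in usual care.
- Apparent risk ratio: 1 / s, which does not depend on p or on arm size.
- Spurious difference: p(1 − s).

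With p = 9%, the rate that Background and rationale cites for rehabilitation delayed at least 10 days:

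| s | EMADE events | Usual-care events | Apparent risk ratio | Spurious difference (points) | Chance EMADE shows the higher count |
|---|---|---|---|---|---|
| 100% | 5.4 | 5.4 | 1.00 | 0 | 44% |
| 90% | 5.4 | 4.9 | 1.11 | 0.9 | 50% |
| 75% | 5.4 | 4.0 | 1.33 | 2.2 | 61% |
| 50% | 5.4 | 2.7 | 2.00 | 4.5 | 79% |

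The last column comes from exact binomial probabilities for the two counts; ties account for the remainder at equal detection.

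**5. Sensitivity to the true rate.** At s = 50% the spurious difference is 0.02 × 0.5 = 1.0 point for a true rate of 2%, and 0.16 × 0.5 = 8.0 points for 16%. At 2% the expected counts are 1.2 and 0.6, and the chance of a higher EMADE count rises from 36% to 51%.

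The documents give no value for s. The 9% comes from another study and is not specific to weeks 2 to 6. Here, infections before the 2-week review precede randomisation and some patients at wound risk may be excluded at that visit, so the relevant rate may be lower. The table also applies s to every infection, although the argument concerns minor ones. It shows how the mechanism works and is not an estimate of its size.

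**The case against.** The strongest reply is that this is a condensed article. It says that adverse events are recorded and that reporting procedures exist, and the forms and timing may be set out in the full protocol. That stands: a reader might infer that nothing is done to collect wound problems evenly, or that events in controls go unrecorded, and the article cannot show either. What remains is a feature the article does state, namely unequal contact and a different type of cast. Reporting procedures alone do not make observation equal.

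Second, there is a common look at the ankle after randomisation. At week 6 the cast comes off, x-ray is reviewed and the ankle is measured in both arms. Although it is not called a wound inspection, anything still present or radiographically visible can be found equally then. Controls with symptoms may also present unscheduled. Both points stand, and they narrow the concern to minor or transient problems.

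Third, the objectives contain no safety objective and no test is planned. This limits the consequence, but descriptive counts will still be read as a comparison.

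Fourth, extra visits are part of the intervention, so unequal contact cannot be designed away. That is true, and it is why the remedy lies in reporting. It would be tempting to drop events found only at EMADE sessions from the account. That could hide real harms of the intervention and is not recommended.

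**Conclusion.** The point holds in limited form. As described, scheduled observation between weeks 2 and 6 is 3 contacts against 0, with a removable cast in one arm only. Minor wound complications in that window may therefore be found more often in EMADE, and an undifferentiated count may mix detection with treatment.

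The size is unknown. Under the assumptions shown, the apparent risk ratio with no true difference runs from 1.00 at full detection in controls to 2.00 at 50%.

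A reader might go further and conclude that complication frequencies will differ, or that EMADE will look less safe. The documents do not support that certainty: the artefact is zero if controls' events are all captured, and persistent or radiographic events are equally detectable at week 6. The OMAS primary analysis is not affected. This is a cheap improvement to reporting; it does not undermine the trial's main question.

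**What to change.** In Data processing, where complications are to be described, state that they will be tabulated by:

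- arm;
- time window: weeks 2 to 6, the week-6 review, and after week 6;
- source of detection: EMADE session, common review, or unscheduled presentation.

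Show all events in both arms, and keep those found only at EMADE sessions in the overall table, flagged by source. Beside it, give a between-arm summary restricted to equally ascertained events: wound status at the existing week-6 review, plus any event in either arm that led to treatment or readmission.

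Trial status reports that 111 participants had already joined, so a new form alone would miss many of them. For those already past week 6, take wound status from the clinic notes and say that this was done.

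The cost is a slightly longer safety table and some abstraction from notes. No extra visit or change of care is needed. Abstracted wound status may be less complete than prospectively recorded status, so its completeness should be reported by arm.
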